## Abstract

**Background:**

Historically, patients with metastatic renal cell carcinoma (mRCC) have been offered upfront cytoreductive nephrectomy (CN) followed by systemic therapy. Currently, CN is no longer the standard of care (SOC) based on the randomised phase 3 CARMENA study performed in the vascular endothelial growth factor receptor tyrosine kinase inhibitor era. With the advent of immune checkpoint inhibitor (ICI) combination therapy in first line, the role of CN needs to be reassessed. There is indirect evidence from small retrospective series that deferred CN after ICI combination therapy may lead to better outcomes. To reassess the role of CN, we designed PrimerX, a randomised controlled trial following the Trial within Cohorts (TwiCs) study design. The primary objective of this study is to re-evaluate the benefit of deferred local treatment in the current era of immunotherapy.

**Study design:**

This PrimerX study has been designed as a TwiCs study within the Dutch Prospective Renal Cell Carcinoma (PRO-RCC) cohort. The PRO-RCC cohort includes patients with mRCC and nonmetastatic RCC, and has been set up for prospective collection of long-term clinical data and as an infrastructure for initiating TwiCs studies. The PrimerX TwiCs trial follows a Bayesian adaptive multistage design to allow for early discontinuation due to futility or efficacy. PrimerX has appropriate ethics approval and is registered at clinical.trials.gov (NCT05941169).

**End points:**

The primary clinical endpoint is overall survival, defined as the time from randomisation to death from any cause. The secondary endpoint is the objective response rate within the primary tumour prior to local therapy, as assessed by a computed tomography scan.

**Patients and methods:**

A maximum of 700 patients with synchronous mRCC and absence of progression at metastatic sites following at least 6 mo of standard first-line ICI combination therapy will be assigned randomly to receive local treatment of the primary tumour (experimental arm) or SOC (control arm). The experimental intervention consists of (partial) CN, any form of ablative local therapy, or magnetic resonance imaging guided ablative stereotactic radiotherapy, performed within 6 mo and 1.5 yr after the start of systemic treatment.

## Introduction

1

Renal cell carcinoma (RCC) accounts for 3% of adult malignancies and 95% of renal tumours. In 2020, >430 000 new cases of RCC were diagnosed globally, with almost 180 000 new deaths [1], [2]. According to recent epidemiological data, between 10% and 20% of patients diagnosed annually with RCC present with synchronous metastatic disease and the primary tumour in place [3].

Cytoreductive nephrectomy (CN) was introduced at a time when first-generation immunotherapy was the only systemic treatment available and the median overall survival (OS) for metastatic RCC (mRCC) was <1 yr [4]. In this context, the benefit of CN was estimated to be around 6 mo, based on two trials that formally evaluated the benefit of CN. In both studies, patients were randomised to receive interferon-α (IFN-α) + CN or IFN-α alone. Both studies reported a benefit: a 3-mo survival benefit in a larger US study and a 10-mo survival benefit in a smaller European study [5], [6]. Several hypotheses were proposed to explain why CN might have a beneficial effect: removal of the “immunological sink” [7], reduced production of growth factors and cytokines by the tumour in situ [8], delayed metastatic progression [9], and nephrectomy-activated azotaemia [10] were among the proposed potential mechanisms.

Since then, two trials have been conducted to assess the role and sequence of CN in combination with vascular endothelial growth factor receptor (VEGFR)-targeted therapy.

Firstly, the CARMENA trial randomised patients to receive CN plus sunitinib versus sunitinib alone to assess the benefit of CN in patients receiving vascular endothelial growth factor–targeted therapy [11]. Secondly, the SURTIME trial randomised patients to receive CN followed by sunitinib versus sunitinib followed by CN (“deferred CN”), investigating the role of preoperative VEGFR-targeted therapy in combination with cytoreduction [12]. Together, the CARMENA and SURTIME analyses provide strong evidence that immediate CN has no benefit and should not be performed in intermediate- and poor-risk Memorial Sloan Kettering Cancer Center patients who require sunitinib or an equivalent VEGFR tyrosine kinase inhibitor (TKI), with, respectively, 43% and 11% survival in poor-risk patients. The OS of patients who received immediate CN in both studies was shorter than that of patients who received immediate sunitinib, although not statistically significant.

Notably, the favourable survival outcome observed in the CARMENA control-arm subgroup, which received deferred CN despite randomisation in the control arm, suggests that there may not be an immediate need to perform early CN [11]. In this subgroup, CN was performed at a median duration of 11 mo of treatment (ranging from 7 to 87 mo), suggesting that confirmation of an on-going response through subsequent imaging could serve as a practical approach for patient selection. Despite the CARMENA and SURTIME studies, the question remains whether mRCC patients receiving immediate sunitinib benefit from deferred CN.

The introduction of first-line immunotherapy with nivolumab and ipilimumab in 2019, based on the CheckMate-214 trial, has led to a paradigm shift in the treatment of clear cell mRCC [13]. The study demonstrated superior OS with nivolumab and ipilimumab to that with sunitinib in clear cell mRCC patients with International Metastatic RCC Database Consortium (IMDC) intermediate or poor prognosis. In these patients, most objective responses occurred by 16 wk. In a 5-yr update, the objective response rate in intermediate and poor IMDC risks was 42%, with 11% developing a complete radiological response [14]. In these risk groups, immune checkpoint inhibitor (ICI) combination therapy is now the standard of care (SOC), with sunitinib and other VEGFR TKI monotherapies being reserved for those who cannot tolerate or do not have access to ICIs. Based on the inclusion of up to 30% of patients without prior nephrectomy in the pivotal ICI trials, the major guidelines continue to recommend immediate systemic therapy for patients with synchronous mRCC [15], [16].

With increased availability of ICI combination therapy, a growing number of these patients develop prolonged systemic disease control and are being offered deferred CN [17]. However, the evidence for the benefit of CN in the context of ICI combination treatment is limited. Retrospective series describe improved survival following ICI combination therapy and deferred CN [18]. Complete pathological responses of the primary tumour have been described in 11–13% of patients treated previously with ICIs [19], [20]. Withdrawal of systemic therapy with treatment-free periods of several years has been reported in patients who had a complete response of metastatic sites to first-line ICIs and were rendered disease free by deferred CN [21], [22]. Our own experience with 21 deferred CN cases after nivolumab plus ipilimumab showed very few desmoplastic tissue changes and adverse events, and three (14%) patients with a complete pathological response [19]. Additional indirect evidence comes from genotypic studies investigating metastatic phenotypes in RCC, which have demonstrated that more aggressive clones may develop in the primary tumour over time, potentially leading to rapid progression and early mortality [13]. These potential benefits require prospective randomised testing against the current standard of systemic therapy alone.

Contemporary retrospective data reveal that the majority of patients (up to 75%) with synchronous metastatic disease no longer undergo CN as part of their management [23], [24]. However, the population without nephrectomy has been a minority in the pivotal ICI combination therapy trials (16.6–30.1%) [16], and there is considerable uncertainty regarding how to manage patients in this setting. To reassess the role of deferred CN in the current era of immunotherapy, we designed PrimerX, a randomised controlled trial (RCT) following the Trial within Cohorts (TwiCs) study design.

## Methods

2

### Study design

2.1

The PrimerX study is conducted within the Dutch Prospective Renal Cell Carcinoma (PRO-RCC) cohort [25]. The PRO-RCC cohort includes patients with metastatic and nonmetastatic renal cancer, and has been designed for prospective collection of long-term clinical data, patient-reported outcome measures, and patient-reported experience measures. Furthermore, the PRO-RCC cohort can be used as an infrastructure for initiating TwiCs studies [26]. The PrimerX study follows this TwiCs study design (Fig. 1). In addition, a Bayesian adaptive multistage design is applied to allow for early stopping for futility or efficacy. Synchronous mRCC patients will be randomised to local therapy (deferred CN or any form of local ablative therapy; experimental intervention) or to a control arm that receives the SOC, in principle without CN. The primary objective is to reassess the benefit of deferred CN in the current immunotherapy era, by a preset analysis of the OS clinical endpoint.

**Fig. 1 f0005:**
[figure not shown]
Embedding of PrimerX TwiCs study within PRO-RCC. CN = cytoreductive nephrectomy; PRO-RCC = Prospective Renal Cell Carcinoma; RCC = renal cell carcinoma; TwiCs = Trial within Cohorts.

### Primary and secondary endpoints

2.2

The primary clinical endpoint is OS, defined as the time from randomisation to death of any cause. The main secondary endpoint is the objective response rate in the primary tumour before local therapy, assessed by a computed tomography scan. Other secondary endpoints are long-term follow-up of quality of life (QoL) using the Dutch validated European Organisation for Research and Treatment of Cancer (EORTC) Quality of Life Questionnaire (QLQ-C30) [27] and Clavien-Dindo classification of surgical morbidity [28]. Both follow-up of QoL and surgical morbidity are part of the standard PRO-RCC data collection schedule.

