### Experimental intervention

2.5

The experimental intervention consists of (partial) CN or any ablative local therapy between 6 mo and 1.5 yr after the start of systemic treatment. All types of ablative local therapies are allowed as a substitute for CN, including magnetic resonance imaging–guided stereotactic radiation. The patients’ physician chooses the treatment plan and the modality used for tumour ablation. Randomisation occurs after at least 6 mo of ICI combination therapy, as stated in Figure 2. Patients who discontinue their first-line treatment due to progression at metastatic sites in the timeframe between randomisation and local therapy are disqualified for local treatment but continued in the TwiCs study in order to be part of the intention-to-treat (ITT) analysis. The same applies for patients who are randomised to the experimental arm but who refuse local treatment. All these patients will be treated according to the SOC. Patients in the experimental arm will be asked for additional sampling of blood after the local intervention.

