### Sample size calculation and Bayesian adaptive design

2.7

Estimation of the median OS of the selected subcohort for PrimerX is not trivial. Based on the CARMENA trial, synchronous mRCC patients treated with sunitinib without CN have median OS of 18.4 mo. All CARMENA patients were treated with VEGFR TKIs only, as ICI combination therapy was not available at the time. In these patients, a reduction in the hazard of death of 20–40% (if they would have been treated with ICI combination therapy, based on the CheckMate-214 study) would have resulted in median OS of 24–28 mo. This is in line with the post hoc OS analysis of mRCC patients with the primary tumour in place in the CM-214 study [30]. This demonstrated median OS of 26.1 mo (95% confidence interval [CI] 14–35 mo) for the ipilimumab + nivolumab arm versus 14.3 mo (95% CI 9.7–23 mo) for the sunitinib arm.

We therefore assume that the median OS for IMDC intermediate/poor-risk synchronous mRCC patients may be up to 28 mo. As in the PrimerX study patients with early systemic disease progression (within 6 mo) are excluded from participation, we estimate that the remaining patients have median OS of 36 mo, when treated with the SOC. The median OS of 36 mo comes down to an event rate per week (lambda) of 1 – (0.5^[1/156 wk]) = 0.0044. We believe that a meaningful deferred local therapy should reduce the hazard of death by at least 25% compared with the SOC (hazard ratio [HR] of 0.75), that is, a 12-mo survival benefit. This would balance the additional treatment burden of local therapy and would result in a median excess in OS of 48 mo in the experimental arm. Furthermore, we estimate that one out of six patients (15%) who are randomised to the experimental arm will refuse any form of local therapy and will therefore be treated by the SOC instead. This noncompliance reduces the measured benefit in an ITT analysis. In addition, a number of patients in the control arm will undergo CN. This also reduces the measured benefit. Based on our 2018–2020 IKNL dataset, we estimate that such “control dilution” will occur in approximately 7% of the cases, as over this period 60 out of 754 synchronous mRCC patients underwent deferred CN. Both noncompliance and control dilution reduce the anticipated HR from 0.75 to 0.7975. After correcting for control dilution, the lambda of the control arm drops from 0.0044 to 0.0043.

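### The only named complication endpoint and its between-arm test cover surgical morbidity, although the experimental arm may receive ablation or stereotactic radiotherapy instead of surgery

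*Protocol article*

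**What the plan says.** Section 2.2 of the protocol article (Primary and secondary endpoints) lists overall survival as primary and response in the primary tumour as the main secondary endpoint. The other secondary endpoints are quality of life by QLQ-C30 and "Clavien-Dindo classification of surgical morbidity". On the data source it states: "Both follow-up of QoL and surgical morbidity are part of the standard PRO-RCC data collection schedule".

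Section 2.5 (Experimental intervention) defines the intervention more widely than surgery: "All types of ablative local therapies are allowed as a substitute for CN, including magnetic resonance imaging–guided stereotactic radiation". The choice is left open: "The patients’ physician chooses the treatment plan and the modality used for tumour ablation". No expected share or cap for non-surgical treatment is given, and the Discussion presents the breadth as deliberate.

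Section 2.8 (Analysis plan) compares the arms on surgical morbidity by Fisher exact test. It also plans subgroup analyses by kind of local treatment, without naming a harm outcome for them. Section 2.7 justifies the target hazard ratio of 0.75 partly by burden: "This would balance the additional treatment burden of local therapy".

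**The concern.** The trial randomises to local therapy of any kind, but its one complication endpoint is worded for one kind. A patient who has stereotactic radiotherapy has no operation, so it is unclear what a site would enter under surgical morbidity. If complications of ablation and radiotherapy do not count, the Fisher test no longer describes the intervention that was randomised.

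The gap would not be even across arms. The local therapy foreseen in controls is deferred nephrectomy (section 2.6; about 7% in section 2.7), which the endpoint covers. Non-surgical local therapy is described only for the experimental arm, so under-recording would make that arm look safer.

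What is at stake is the morbidity result that readers will weigh against any survival gain. The article itself makes that trade-off when it sets the target effect. Complications that are not collected cannot be recovered by a later analysis plan.

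**Working it through.** The plan gives no morbidity rate, so there is no figure of its own to reproduce. The check has two parts.

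**1. Scope, section against section**

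- Intervention (2.5): partial or total nephrectomy, or any ablative therapy including stereotactic radiation.
- Complication endpoint (2.2): surgical morbidity.
- Test (2.8): surgical morbidity, between arms. Section 2.8 puts the analyses on an intention-to-treat basis, so all randomised patients would stay in the denominator.
- Data source (2.2): the cohort schedule, for which only quality of life and surgical morbidity are named.

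Endpoint, test and data source use the narrower term; the intervention uses the wider one. No sentence says that the grading also applies to ablation or radiotherapy, and none says that it does not.

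**2. Illustrative size under the literal reading**

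Inputs from section 2.7: at most 350 patients per arm, 15% refusal in the experimental arm, 7% nephrectomy in controls. Assumed, because not given: non-surgical share s of 10%, 30% or 50%; surgical complication rate 20%; non-surgical complication rate r of 5% to 20%.

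- Treated in the experimental arm: 350 × 0.85 = 297.5. This ignores patients who progress before local therapy, so it is on the high side.
- Complications outside the endpoint: 297.5 × s × r.
- Recorded complications: 297.5 × (1 − s) × 0.20.
- Share left out: s·r / [s·r + (1 − s) × 0.20].

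| s | r | Left out | Full rate in arm (of 350) | Recorded rate in arm | Share left out |
|---|---|---|---|---|---|
| 10% | 5% | 1.5 | 15.7% | 15.3% | 2.7% |
| 10% | 20% | 6.0 | 17.0% | 15.3% | 10% |
| 30% | 5% | 4.5 | 13.2% | 11.9% | 9.7% |
| 30% | 20% | 17.9 | 17.0% | 11.9% | 30% |
| 50% | 5% | 7.4 | 10.6% | 8.5% | 20% |
| 50% | 20% | 29.8 | 17.0% | 8.5% | 50% |

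Worked line for s = 30%, r = 20%: left out 297.5 × 0.30 × 0.20 = 17.85; recorded 297.5 × 0.70 × 0.20 = 41.65; full rate (41.65 + 17.85)/350 = 17.0%; recorded rate 41.65/350 = 11.9%.

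Controls on the same assumption: 350 × 0.07 × 0.20 = 4.9 complications, or 1.4%, all after nephrectomy and so all within the endpoint. In the worked line the difference between arms is 17.0 − 1.4 = 15.6 percentage points in full, but 11.9 − 1.4 = 10.5 as recorded.

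**The case against.** Four objections have weight.

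- **Recording is not described.** A reader might infer that radiotherapy toxicity will be entered as none. The article does not say so. Sites might grade it on the same scale, mark it not applicable, or drop the patient from the denominator. This objection stands: coverage is undefined, not shown to be absent, and the table above holds only for the literal reading.
- **Other endpoints see part of the burden.** A reader might infer that harm from non-surgical treatment is not captured at all. That goes too far. QLQ-C30 is collected whatever the modality, and the primary endpoint is "The primary clinical endpoint is OS, defined as the time from randomisation to death of any cause", so fatal complications count. Yet survival sees only fatal harm, and a quality-of-life questionnaire does not grade complications; neither replaces the Fisher comparison.
- **This is a condensed article.** Adverse-event collection may well be set out in the full protocol, and a data and safety monitoring board is mentioned. Absence of a safety section is therefore no finding. What remains is that the endpoint and test the article does state do not fit the intervention it states.
- **No decision uses morbidity.** Stopping rests on the posterior probability for the hazard ratio, and efficacy on the log-rank test for survival. The burden argument in section 2.7 only sets the target in advance. A reader might infer that any comparison of modalities would be wrong, but no harm comparison by modality is specified. Both limits stand.

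The non-surgical share may also be small. The eligibility table requires surgical candidates, and the Discussion calls nephrectomy the gold standard and links ablation with smaller tumours. It also notes marked downsizing under immunotherapy, which leaves the share open.

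**Conclusion.** The point holds as a mismatch between a stated endpoint and a stated intervention. As worded, the only complication endpoint and its between-arm test measure surgical morbidity, while the randomised intervention is local therapy of any kind. On the literal reading, with all randomised patients in the denominator, the experimental arm's morbidity is understated.

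The size is conditional. It runs from about 3% of local-therapy complications (10% non-surgical share, 5% complication rate) to 50% (50% share, same 20% rate as surgery). All shares and rates are assumptions. If sites already grade every modality, the understatement disappears and only the wording needs correcting.

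The primary survival analysis, the sample size and the stopping rules are untouched. This is a worthwhile, low-cost improvement to a secondary endpoint; it does not threaten the main result.

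**What to change.** In sections 2.2 and 2.8, replace surgical morbidity by morbidity of any local therapy, and run the Fisher comparison on that endpoint:

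- Grade it on a scale that applies to every modality, for example CTCAE grade 3 or higher, for each patient in either arm who receives local therapy.
- Fix one assessment window from the start of local therapy and add a later time point for delayed toxicity.
- State how patients without local therapy enter the between-arm comparison.
- Keep Clavien-Dindo as a description for surgical patients, and report morbidity by modality.

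If the present grading is already meant to cover ablation and radiotherapy, one sentence saying so would settle the scope; the window and the later time point would still be worth stating.

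The cost is a change to the endpoint and analysis text and somewhat more data entry for treated patients. The cohort's forms and visit schedule are not shown, so the sponsor should check whether the later time point fits existing follow-up.

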### Exploratory outcomes

2.3

For one of the exploratory outcomes, fresh-frozen and paraffin-embedded tissue of pretreatment biopsies and post-treatment tissue obtained at either partial or total nephrectomy will be collected, as well as peripheral blood before and during treatment, to analyse the immune compartments in the peripheral blood and in the tumour, especially tumour infiltrating lymphocytes and myeloid-derived suppressor cells (MDSCs). In detail, we will examine the intratumour alteration of tumour infiltrating CD8, CD4, and NK(T) cells (CD56+ and CD3+/–) and the distribution of these NK cells in the tumour. Furthermore, Treg (CD3+CD4+FoxP3+), tumour-associated macrophages (TAM, CD68+, CD16+/–, and CD163+/–), and MDSCs (CD11b+, HLA-DR, and CD33+), differentiating between pro- and anti-inflammatory M1 and M2 subtypes, will be assessed. In addition, genomic profiling (Illumina assay) and the analysis of effects on angiogenesis will be investigated.

### Eligibility criteria

2.4

At enrolment in the PRO-RCC cohort, patients are asked to provide informed consent for prospective collection of clinical, survival, and QoL data. In addition, on entry in the cohort, we ask patients to consent for possible future randomisation in TwiCs studies (staged informed consent procedure) [29]. Herein, patients are informed that, when a TwiCs study to investigate the efficacy of a new experimental intervention is initiated, they will be offered that experimental intervention if they are selected randomly for the experimental intervention group. They are also advised that they will not be informed about the TwiCs study when selected randomly for the control group but that their data will be used as in the trial context. Patients within the PRO-RCC cohort who meet the PrimerX inclusion criteria, as mentioned in Table 1, form a subcohort of eligible patients. Within this subcohort, patients without progression at metastatic sites, with the primary tumour in site (irrespectively of the size of the tumour), following at least 6 mo of any of the standard first-line ICI combination therapies, are allocated randomly to either the experimental arm or the control arm in a 1:1 ratio, until the calculated sample size is reached or early stopping rules are met. Patients who have progression in the primary tumour only are also eligible for trial participation. Since patients are randomised at different time points, between 6 and 18 mo after the start of systemic treatment, the timing of randomisation is added as a variable when conducting the analysis.

**Table 1 t0005:** Inclusion criteria

Male or female patients age ≥18 yr
Signed and written informed consent obtained; note: written and signed informed consent will be obtained before any study procedures, including study‐specific-screening procedures
Informed consent obtained for being offered future experimental interventions within the PRO-RCC project
Histologically confirmed diagnosis of metastatic clear cell, papillary, or chromophobe renal cell carcinoma of intermediate to poor risk, including sarcomatoid features
World Health Organization performance status of 0–1
Surgical candidates based on surgeon and anaesthetist assessment
Treatment with an IO combination (IO + IO or IO + TKI) as standard of care for metastatic RCC for at least 6 mo
Absence of progression at metastatic sites at the time of identification (6 mo after the start of systemic first-line treatment)
Primary tumour in situ
Participation in the PRO-RCC prospective cohort

IO = immune oncology; PRO-RCC = Dutch Prospective Renal Cell Carcinoma; RCC = renal cell carcinoma; TKI = tyrosine kinase inhibitor.

Patients who are randomised to the experimental arm will be counselled by their treating physician for participation in the experimental arm. If these patients accept the intervention, they are asked to sign an additional informed consent form containing all information regarding the PrimerX study, as part of the staged informed consent procedure [29]. Patients who refuse the offered experimental intervention will continue to receive the SOC. Patients randomised to the control arm will receive no additional consent for the TwiCs study, and thus not informed about the experimental intervention or about their participation in the study as controls (Fig. 1), based on their consent upon entry in the cohort. Patients randomised to the control arm will receive the SOC.

